### Demographic and Psychological Assessment

Demographic information, such as age, place of birth, education, occupation, civil status, household income, housing characteristics, as well as medical and family history, will be collected at baseline. A form will be filled in by the participant, assistance from the trained research staff will be provided if it is required.

The psychological tests will be administered at baseline within the first 15 days of participation. A battery of self-report questionnaires has been chosen to assess for a history of childhood trauma (Adverse Childhood Experiences Assessment [ACEs]) [68], the presence of depression or depressive symptoms (Beck Depression Inventory [BDI-II]) [69], anxiety and stress (Beck Anxiety Inventory [BAI-II]) [70], sleep disorders (Pittsburgh Sleep Quality Index [PSQI]) [71], and short-term memory (Wechsler Adult Intelligence Scale IV [WAIS-IV] subtests: Digit Span and Letter-Number Sequencing) [72]. Substance use–specific tests will aim to determine the type of substance, frequency and quantity of used drugs (Alcohol, Smoking and Substance Involvement Screening Test [ASSIST]) [73], level of substance craving (Mannheimer Craving Scale [MaCS]) [74], as well as the stage or frame of mind of the individual starting the therapeutic process (University of Rhode Island Change Assessment Scale [URICA]) [75].

To obtain a comparative measurement after treatment, depression, anxiety and stress, sleep disorders, short-term memory, stage of change and craving, will be reevaluated within fifteen days before the sixth month period of digital tracking ends (Figure 3).

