### Timeline

This study will include 2 types of observations: continuous passive monitoring and active surveys conducted at specific time points. Passive monitoring will occur continuously for 6 months in both groups, followed by an additional year for participants with SUD after their discharge from the treatment facility. Active surveys will be conducted at three time points: (1) baseline session or baseline, (2) 3 months after baseline, and (3) 6 months after baseline.

For digital monitoring purposes, smart bands provided to participants will be synchronized with a smartphone at the baseline session. Psychological assessment will be conducted within the first 15 days after baseline. Retesting will take place during the 15 days prior to the 6 months after baseline. Emotional reactions to cravings will be assessed at two points: (1) 3 months after baseline and (2) at 6 months after baseline (Figures 1A-1F).

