### Instruments

The study instruments that will be used in this protocol to measure each assessment category referred to in the timeline (Figure 1), are presented in Table 1.

**Table 1 table1:** Study instruments.

Instrument	Period				
	Baseline	3 Months	6 Months	18 Months	Continuous
Wearable: Xiaomi Redmi Smart Band 8^a^	✓	✓	✓	✓ ^b^	✓
Demographic survey^c^	✓				
The Adverse Childhood Experiences Assessment (ACEs)^d^	✓				
The University of Rhode Island Change Assessment Scale (URICA)^d^	✓				
The Alcohol, Smoking and Substance Involvement Screening Test (ASSIST)^d^	✓				
The Beck Depression Inventory (BDI-II)^d^	✓				
The Beck Anxiety Inventory (BAI-II)^d^	✓				
The Pittsburgh Sleep Quality Index (PSQI)^d^	✓		✓	✓^b^	
Wechsler Adult Intelligence Scale IV (WAIS-IV): Digit Span and Letter-Number Sequencing subscales^d^	✓		✓		
Emotional Pictures Database (EmoMadrid)^e^		✓	✓		
Mannheimer Craving Scale (MaCS)^e^	✓	✓	✓		
Automatic facial emotion recognition software (FER)^e^		✓	✓		

^a^Digital measurement of biomarkers.

^b^Substance use disorder group only.

^c^Demographic assessment.

^d^Psychological assessments.

^e^Emotional state during craving assessment.

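### Table 1 leaves BDI-II, BAI-II and URICA out of the month-6 retest that the text requires, conflicts with the Timeline at 18 months, and like the Timeline schedules no substance-use measure after baseline

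*Protocol article*

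**What the plan says.** **Retest.** The Demographic and Psychological Assessment section lists six constructs: "depression, anxiety and stress, sleep disorders, short-term memory, stage of change and craving, will be reevaluated within fifteen days" before the six-month tracking period closes. The stated purpose is a comparison after treatment. The Timeline gives the same window: "Retesting will take place during the 15 days prior to the 6 months after baseline". The Abstract also has everyone reassessed at month 6, and the Figure 1 caption (panel A) has the battery applied twice.

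**Instrument table.** The Instruments section introduces Table 1 as follows: "The study instruments that will be used in this protocol to measure each assessment category referred to in the timeline (Figure 1), are presented in". Of the psychological instruments, only PSQI and the WAIS-IV subscales carry a month-6 tick. MaCS, filed under craving, is ticked at baseline, 3 and 6 months. BDI-II, BAI-II, URICA, ACEs and ASSIST are ticked at baseline only. The 18-month column holds the smart band and PSQI, both for the SUD group only.

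**Survey time points.** The Timeline states: "Active surveys will be conducted at three time points: (1) baseline session or baseline, (2) 3 months after baseline, and (3) 6 months after baseline".

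**Outcome labels.** The Output section separates early relapse (use in the first 6 months after discharge), late relapse (use after that and before 18 months post discharge) and one-year maintenance (abstinent at the end of an 18-month period after recovery).

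**The concern.** The text and the table give different month-6 batteries. A questionnaire not given in its 15-day window cannot be given later, so the conflict matters while participants are still reaching month 6.

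The second issue is the outcome. Relapse latency supplies three of the five output labels, and each needs to be known as a fact and, for two of them, as a date. The only listed instrument that records type, frequency and quantity of use is ASSIST, and it is scheduled once, at baseline. A reader of this article cannot tell what contact or measure produces the label on which the model will be trained and tested.

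**Working it through.** No stated figure needs to be reproduced; the check sets the schedule statements side by side.

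**Step 1. Month-6 retest.** Constructs come from the retest sentence, their instruments from the same section, and ticks from Table 1.

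| Construct | Instrument | Baseline tick | Month-6 tick |
|---|---|---|---|
| Depression | BDI-II | yes | no |
| Anxiety and stress | BAI-II | yes | no |
| Sleep | PSQI | yes | yes |
| Short-term memory | WAIS-IV subscales | yes | yes |
| Stage of change | URICA | yes | no |
| Craving | MaCS | yes | yes |

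Scheduled: 3 of 6. Missing: 6 − 3 = 3, or half. ACEs and ASSIST are not named in the retest sentence, so their baseline-only ticks do not contradict it.

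**Step 2. 18 months.** Table 1 has PSQI, a self-report questionnaire, at 18 months in the SUD group. The Timeline's list of three survey points ends at month 6, and the Figure 1 caption allows the battery two time points. These cannot all be right.

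**Step 3. Substance use after baseline.** Instruments described as measuring use: 1 (ASSIST), with 0 ticks after baseline. MaCS measures craving and stops at month 6. At 18 months the two entries are the band and PSQI. The features in Table 2 (activity, heart rate, sleep, rhythm, oxygenation, stress) do not measure use, and they are model inputs.

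**Step 4. Follow-up against label window.** The Abstract gives 18 months in total for SUD participants, 6 in rehabilitation and 12 after discharge; the Timeline likewise adds one year after discharge. The Output labels run to 18 months post discharge. Difference: 18 − 12 = about 6 months of label window with no planned monitoring.

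**Step 5. Urgency.** By June 2025, 18 + 17 = 35 participants were enrolled and some 3-month data were in processing (Results). If that status also dates from June, the earliest had their baseline by about March 2025 and reach month 6 by about September 2025. The date of first enrolment is not given.

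**The case against.** **On the table.** The article never calls Table 1 the operational schedule, and the retest is stated consistently in the Abstract, the Timeline, the Figure 1 caption and the assessment section. The likeliest explanation is missing ticks. Figure 3, cited for the retest, is not shown and might carry the full battery. A fault in reading the table is possible, but the PSQI, WAIS-IV and MaCS rows keep their ticks in the expected columns, so it is unlikely. It stands that the harm is conditional. A reader might infer that half the change scores will be lost; the documents support only that they could be, if staff follow the table. No lost data are reported. Nor can it be said that the first participants reach month 6 in July 2025: January 2025 is when recruitment opens, not a reported first enrolment.

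**On relapse.** This is a condensed article. Every row of Table 1 is classed as a biomarker, demographic, psychological or craving assessment, which are the predictor profiles; the table has no outcome category. The Withdrawal Criteria and Data Exclusion sections presuppose that relapse is identified, since it ends participation and data are excluded when its timing is unknown. This stands too. A reader might infer that the study cannot detect relapse, or that undisclosed relapses will be labelled as maintenance. The article supports neither: it is silent on the method.

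**On repeating ASSIST as the remedy.** It is a self-report tool, so undisclosed use may stay undisclosed, and the article describes it as giving type, frequency and quantity rather than a date. Repeating it alone would not date a relapse.

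**Conclusion.** The point holds in three parts of unequal weight.

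1. **Firm.** Table 1 contradicts the retest sentence for 3 of 6 constructs and contradicts the Timeline on the 18-month questionnaire. This rests only on the article's own statements. A fuller document could show which version is intended, but the two published versions would still disagree.
2. **Firm.** Planned follow-up ends about 12 months after discharge, while the labels run to 18 months, a difference of about 6 months. This takes the Abstract and the Timeline at their word on the post-discharge year.
3. **Limited.** Neither Table 1 nor the Timeline schedules a substance-use measure after baseline, although the relapse labels rest on use after discharge. This is a statement about the published schedule, not about the whole study. Any resulting misclassification cannot be sized from the article.

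The correction should be made before more participants pass month 6.

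**What to change.** - **Table 1:** add month-6 ticks for BDI-II, BAI-II and URICA, and check Figure 3 and the site's working schedule against the corrected table. This costs a table correction; the text already plans these retests.
- **Timeline:** add the 18-month contact for the SUD group, where PSQI is already listed, and adjust the Figure 1 caption to match.
- **Relapse:** state how the fact and date of post-discharge use are established, or cite the document that does. At the month-6 and 18-month contacts, record self-reported use and the date of first use. The date is a new item, needed to separate relapse before and after 6 months post discharge. It costs a few extra minutes and no new visit. Recall over about 12 months and self-report bias remain and should be named as limitations.
- **Follow-up window:** reconcile the end of follow-up in the Abstract and the Timeline with the label window in the Output section. Until then, the 18-month contact falls about 6 months short of the end of that window, and the new item cannot support labels beyond it.

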**Figure 3 figure3:**
[figure not shown]
Flowchart of the psychological test battery. WAIS-IV: Wechsler Adult Intelligence Scale IV;.

### Emotional State During Craving

Given the significance of craving in SUD, a profile of the ESDC will be developed. Participants will be shown images from the Emotional Picture Database (EmoMadrid), designed by CEACO, which will be used as stimuli to elicit an emotional response [76]. Participants will be recorded all throughout the test, and Facial Emotion Recognition (FER) software. Software will provide an objective, real-time measure of participants’ emotional expressions, which we will analyze in conjunction with their self-reported “Emotional State during Craving” data. The FER software is a personal script written in python, which automatically detects emotions by analyzing changes of facial expression of dataset that consists of 48×48 pixel grayscale images (32,298 images) of faces (FER-2013). Craving levels will be measured both before and after the test.

An experimental setup will be arranged to ensure optimal conditions for the test. This setup will include a white screen for image projection, an HD camera for recording the participant, and a controlled environment with low lighting and sound insulation to minimize distractions. A trained researcher will administer the test in this environment.

At the start of the experiment the FER software will be activated and participants will respond to items 9 to 11 of the MaCs scale (Table 1), which assesses craving-related anxiety levels, the effort required to resist urges, and impulses to consume substances. Following this brief questionnaire, the instructions for the experiment will be presented both visually and verbally to ensure the participant's full understanding.

A modified version of the protocol has been designed to suit the characteristics of the study population. Fifty images have been selected and categorized as positive, negative, neutral, or substance-use-related. These images have been further customized to align with the substance use profile of the participant group. Each image will be displayed for 1 second, after which participants will score it based on valence and activation. Once a score is provided, the next image will be shown. The procedure will be divided into 2 sets of 25 images, with a 30-second rest period between sets.

After the image presentation, participants will be reassessed using the same 3 MaCs scale items. In addition, they will be asked whether they experienced any changes in their emotional state after viewing the images and to provide a qualitative description of any observed shift (Figures 4A-4D).

All data obtained from the FER analysis, MaCS EMA, the EmoMadrid emotional response assessment and physiological data obtained by the smart band, will be used to observe the relationship between exposure to emotional and substance use visual stimuli, emotional response and craving.

**Figure 4 figure4:**
[figure not shown]
Flowchart of emotional reaction to craving assessment. Steps of the brief craving assessment, in addition to a modified version of the emotional pictures database for valence and activation, including a sample of the chosen images of each category. (A) Positive images (n=15). (B) Negative images (n=16). (C) Neutral images (n=10). (D) Substance use-related images (n=9).

### Statistical Analysis

Statistical analysis will be conducted using R-Studio IDE (version 4.3.1; Posit PBC), Prism GraphPad (version 9, GraphPad Software Inc), and MATLAB (version R2025a, MathWorks Inc). A descriptive analysis of normality (Shapiro-Wilkin normality test) means and medians, SD and error, variance (ANOVA or Kruskal-Wallis tests) will be performed. Correlation analyses (Spearman or Pearson) will be conducted to gain a preliminary understanding of the interactions between variables, as well as using time series analysis descriptive models to identify patterns, trends and cycles of activities by participants, and by groups. MATLAB will be used for advanced data processing and visualization, ensuring robust and comprehensive analysis.

### Data Exclusion

Missing data will be addressed through imputation. If more than 20% of daily data samples are missing, they will be excluded. For missing data below this threshold, linear interpolation and neighbor mean imputation (k-nearest neighbor) will be applied during preprocessing using MATLAB.

The quality of data collected from the smart band will be assessed by correlating heart rate at randomly selected timestamps with oxygen saturation, activity levels, self-reported exercise, and sleep type during sleep hours. If atypical correlations are identified, 10 data points before and after the anomaly, along with 5 additional randomly chosen timestamps, will be reviewed. A day with more than 20% of faulty measurements will be excluded from the dataset.

Data will also be excluded in cases of device misuse, such as exchanging the device with other participants or nonparticipants, switching the wearing side without prior notice, or removing the device for more than 5 hours without informing the research team.

If the total sum of missing and excluded data exceeds 20% of the 6-month period, the participant's data will be removed from the study. Finally, for SUD participants, any measurements obtained during periods of substance use will be excluded, and their participation in the study will be terminated.

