### Digital Measurement of Biomarkers

The Xiaomi Redmi Smart Band 8 will be worn on the user's nondominant hand, positioned 2 cm below the wrist bone and secured at a comfortable level, as instructed by the user manual. The device will be worn for a minimum of 22 hours per day, allowing for an anticipated loss of up to 2 hours of data due to activities such as recharging the device, synchronization with a smartphone, showering, and other routine tasks.

Physiological data, including heart rate (HR), peripheral capillary oxygen saturation, physical activity, stress, and sleep, will be collected using the device's shortest available measurement intervals. Data will capture periods of both high and low activity, during self-reported exercise, regular physical activity, and rest, and will identify any abnormalities in activity patterns.

Data synchronization, which facilitates upload to the associated Xiaomi account, will occur every 72 hours for all participants during the 6- or 18-month study period, as applicable. This data will be downloaded, preprocessed, and stored securely on an encrypted external hard drive and the institution's server for access by authorized research staff within 48 hours (Figures 2A-2E). Participants will receive a reminder notification if synchronization is not completed within 5 days.

Raw data will be used to compute digital the physiological features proposed in a MLM study by Rykov et al, [30] (Table 2).

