**Figure 2 figure2:**
[figure not shown]
Scheme of smart band data retrieval. (A) Data from the smart band Xiaomi Redmi Smart Band 8 via Bluetooth to the smartwatch it’s been linked to for synchronization. (B) Through the Xiaomi app Mi Fitness, the data of the monitored period will be uploaded to the account’s cloud to be downloaded by the researchers. (C) Raw data will be extracted, labeled, and preprocessed. (D) All data will be saved in an assigned encrypted server, property of Universidad de Guadalajara. (E) Alternatively, a second copy will be done on an encrypted external hard drive.

**Table 2 table2:** Summary of raw measurements and physiological features.

	Raw data	Physiological features
Physical activity	Calories, steps, vitality, and time standing up	Daily footsteps, sedentary time, light physical activity, moderate physical activity, and vigorous physical activity
Heart rate (HR)	Beats per minute (BPM), maximum and minimum BPM, and single measure	HR resting HR, daytime HR, nighttime HR, HR delta, and HR root-mean-square successive differences
Sleep	Type of sleep, wake-up time, bedtime, and awake	Coefficient variance, time in bed, total sleeping time, sleep efficiency, sleep onset latency, waking after sleep onset, and sleep midpoint
Rhythm	Activity peaks	Circadian rhythm: COSINOR and nonparametric measurements
Oxygenation	SpO_2_^a^ during daytime, single measures of SpO_2_, and sleep time SpO_2_	—^b^
Stress	Stress level and single stress measurements	—

^a^SpO₂: peripheral capillary oxygen saturation.

^b^Not available.

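### Filling heart-rate gaps by linear interpolation before computing the root-mean-square of successive differences would lower that feature by up to about 16% at the plan's missing-data ceiling

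*Protocol article*

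**What the plan says.** The Data Exclusion section works at the level of samples within a day. Days above a limit are dropped: "If more than 20% of daily data samples are missing, they will be excluded". Below the limit, gaps are filled: "For missing data below this threshold, linear interpolation and neighbor mean imputation (k-nearest neighbor) will be applied during preprocessing using MATLAB". A matching limit applies to the participant: "If the total sum of missing and excluded data exceeds 20% of the 6-month period, the participant's data will be removed from the study".

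Digital Measurement of Biomarkers says of the derived variables: "Raw data will be used to compute digital the physiological features". The Figure 2 legend gives the data flow: "Raw data will be extracted, labeled, and preprocessed". The heart-rate row of Table 2 lists "HR resting HR, daytime HR, nighttime HR, HR delta, and HR root-mean-square successive differences". Samples "will be collected using the device's shortest available measurement intervals", with no interval in seconds or minutes. Some daily loss is expected, "allowing for an anticipated loss of up to 2 hours of data due to activities such as recharging the device" and similar routine tasks.

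The article does not say how many neighbours are used, whether neighbours are adjacent times or similar records, which method fills which gap, or whether filled samples enter RMSSD.

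**The concern.** RMSSD measures sample-to-sample variation. A straight line drawn across a gap has almost none, so each interpolated stretch adds differences that are too small. The more a participant's record has been filled, the lower the computed RMSSD, whatever the true physiology. The feature then carries information about wear time as well as heart rate.

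This would be routine, because the plan expects daily gaps for charging and showering and fills them. If missingness is also related to group or to outcome class, the filter-based feature selection described under Data Preprocessing could keep RMSSD for the wrong reason.

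**Working it through.** **Inputs from the article.** Filling by linear interpolation and by neighbour mean; at most 20% of a day's samples filled; anticipated loss 2 h of 24 h, that is 2/24 = 8.3%. The article gives no figure for the size of this distortion, so there is none to reproduce.

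**Assumptions.** One sample per minute (1440 a day); heart-rate noise from independent to strongly autocorrelated (first-order autoregressive, coefficient 0, 0.5, 0.9 or 0.98); gaps as scattered single samples, 10-minute runs or one block; 5-20% missing. None of these is in the article.

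**Step 1: direction under linear interpolation.** A gap of m samples spans m+1 successive differences d. Interpolation replaces their sum of squares, Σd², by (Σd)²/(m+1). By the Cauchy-Schwarz inequality this cannot exceed Σd². Filled RMSSD therefore never exceeds complete-series RMSSD, at any sampling interval.

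**Step 2: size under linear interpolation.** Let f be the missing fraction.
- Independent noise: the expected share of squared differences lost is f(m+2)/(m+1). It is largest for isolated single gaps (m = 1), at 1.5f, and tends to f for long gaps.
- Very strong autocorrelation (the random-walk limit): the share lost is f.

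The ratio of filled to true RMSSD thus lies between about √(1−1.5f) and √(1−f). Simulation of 60 days of 1440 samples agrees:

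| Missing f | √(1−1.5f) | √(1−f) | Simulated range |
|---|---|---|---|
| 5% | 0.962 | 0.975 | 0.962-0.975 |
| 8.3% | 0.935 | 0.957 | not run |
| 10% | 0.922 | 0.949 | 0.923-0.949 |
| 15% | 0.880 | 0.922 | 0.885-0.922 |
| 20% | 0.837 | 0.894 | 0.846-0.896 |

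**Step 3: the neighbour-mean method, under its possible meanings (simulated filled/true ratio).**
- Mean of the 5 nearest samples in time: 0.970-0.987 at 5% missing and 0.877-0.951 at 20%. Always downward.
- Nearest neighbours across days, k = 5, at 20% missing: 0.915-0.936 for one block; from 0.918 (independent noise) to 2.66 (coefficient 0.98) for scattered gaps.
- Nearest neighbours across days, k = 1, at 20% missing: 1.00 to 3.40.

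A value borrowed from another record can jump against its observed neighbours, and this is how the sign reverses.

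**Step 4: the alternative.** RMSSD from adjacent observed pairs only gave ratios of 0.997 to 1.003 in every scenario from 5% to 20% missing.

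**The case against.** **The order of processing is inferred.** No sentence says that filling precedes feature computation or that filled samples enter RMSSD, and a condensed article may leave such detail to a fuller plan. This stands as a limit on certainty. Still, the exclusion rule counts samples within a day, imputation belongs to preprocessing, and the Figure 2 legend applies preprocessing to the extracted raw data. Filling first is the natural reading.

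**Standardisation.** All wearable data are to be z-scored, so a proportional shrinkage common to everyone cancels. That is right: only differences in missingness between participants can matter to the model.

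**Group differences.** A reader might infer that missingness will differ between patients and controls, because centre staff synchronise the patients' bands and controls handle their own. The documents do not support that. Who synchronises a band is not who wears it, the wear minimum and the 72-hour synchronisation interval apply to all, and the same 20% limits hold in both groups. If one assumed 5% missing in one group and 15% in the other, long gaps would give 0.975 against 0.922, a spurious gap of 1 − 0.922/0.975 = 5%; that contrast is purely an illustration. Moreover, the duration and relapse labels are defined within patients, so a patient-control contrast bears only on the separate task of telling the two groups apart.

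**Ceiling.** Study Setting equates 2.4 hours with 20% of the day, but 2.4/24 = 10%. If 10% is the working limit, the shortfall under interpolation is 5-8%, not 10-16%. The article leaves this open.

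**Conclusion.** The point holds for one feature, on the natural reading that gaps are filled before features are computed. Under linear interpolation the downward direction is certain. The size is about 2.5-4% at 5% missing, 4-6% at the anticipated 2 hours a day, 5-8% at 10% and 10-16% at 20%, over the assumed range of autocorrelation and gap lengths. It grows roughly, not exactly, in proportion to missingness.

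Two stronger readings are not supported. One is that both filling methods must bias the feature downwards: nearest-neighbour filling from similar records can leave it unchanged or raise it, so the sign depends on a choice the article does not state. The other is that circadian indices suffer in the same way: Table 2 names only COSINOR and nonparametric measures, with no index identified as built on successive differences.

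The effect on the model depends on whether missingness is related to group or outcome. The article gives no data on that and no between-person spread of RMSSD, so no effect on the AUC can be stated. This is a low-cost improvement to one feature among many, not a threat to the study as a whole.

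**What to change.** State in Data Exclusion, or beside Table 2, that RMSSD is computed from pairs of adjacent observed samples only and that imputed samples are left out of it. Carry the daily wear fraction as a quality variable, so that any link between wear and group or outcome can be seen. Where neighbour-mean imputation is kept for other purposes, state the number of neighbours and whether they are adjacent times or similar records.

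The observed-pairs estimate is close to unbiased when gaps are unrelated to heart-rate variation; otherwise it describes worn time only, and the article should say so.

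The cost is a small change to the MATLAB preprocessing and no new data. It is timely: the Results section places the device data at the labelling and preprocessing stage.

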#### Withdrawal Criteria

Participants will be withdrawn from the study under the following circumstances: failure to use or misuse of the smart band for more than 5 consecutive days or exceeding 20% of the six-month period will result in the cessation of monitoring, with participants being notified, the device retrieved, and the data discarded. Relapse in substance use for the SUD group or the onset of addictive behavior for controls will also lead to immediate withdrawal; if the exact timing of such behavior cannot be determined, the corresponding data will be excluded. Finally, participants who voluntarily drop out of the study or request the removal of their data will be withdrawn, and their data will be discarded.

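### The 20% participant-removal limit does not define what it counts, can remove a man whose band record is largely complete, and deletes data that do not depend on the band

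*Protocol article*

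**What the plan says.** Data Exclusion works at two levels.

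- **Day, missing data:** "If more than 20% of daily data samples are missing, they will be excluded". Smaller gaps are kept and filled: "For missing data below this threshold, linear interpolation and neighbor mean imputation (k-nearest neighbor) will be applied".
- **Day, faulty data:** "A day with more than 20% of faulty measurements will be excluded from the dataset".
- **Participant:** "If the total sum of missing and excluded data exceeds 20% of the 6-month period", all data of that participant are taken out of the study.

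Three other sections bear on the same quantity.

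- **Withdrawal Criteria** has its own 20% limit. It applies to non-use or misuse of the band, "exceeding 20% of the six-month period will result in the cessation of monitoring", and the data are then discarded.
- **Digital Measurement of Biomarkers** requires 22 hours of wear a day, "allowing for an anticipated loss of up to 2 hours of data" for charging, synchronization, showering and the like.
- **Study Setting** repeats the 22 hours but sets a daily loss threshold of 2.4 hours and labels it 20%.

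**The concern.** The participant-level sum has two components, missing data and excluded data. The text does not say whether it is counted in samples, hours or days. It does not say whether a gap that has been imputed still counts as missing, or whether an excluded day counts in full or only for the hours actually lost.

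Taken at face value, a day just over the limit enters as a whole lost day, and the small daily gaps that the plan regards as usable are added on top. The total then no longer follows the amount of data recorded.

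Passing the limit costs more than the band features. As written, the participant's data leave the study, which takes in his demographic form, questionnaires, craving test and outcome label. The protocol treats demographic, psychological, craving and digital-biomarker data as four separate profiles (Outcomes, Profiles), and the outcome labels rest on completion of the program and later abstinence (Output). With a minimum of 25 per group (Sample Size), each man lost is up to 1/25 = 4% of the SUD sample. Selection by adherence could matter if adherence is related to outcome; the documents do not say whether it is.

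**Working it through.** **Inputs.** Daily limit 20% of 24 h = 4.8 h (Data Exclusion). Participant limit 20% of 6 months (Data Exclusion). Routine loss up to 2 h a day (Digital Measurement of Biomarkers). The period is taken as 182 days, an assumption; 180 or 183 days changes the recorded shares by about 0.1 point at most. The limit is then 0.20 × 182 = 36.4 days. The plan gives no calculated figure to reproduce.

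**Literal reading.** Let k be the number of excluded days, b the share lost on an ordinary day and m the share lost on an excluded day.

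- Removed if k + (182 − k)b > 36.4
- Share truly lost = [k·m + (182 − k)b] / 182

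**Ordinary days complete (b = 0).** Removal comes at k = 37, since 37/182 = 20.3%. With 5 h lost on each bad day the true loss is 37 × (5/24) / 182 = 4.2%.

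**Routine loss of 2 h (b = 2/24).** Routine loss alone uses 182 × 2/24 = 15.2 of the 36.4 days. Removal comes at k = 24, since (24 + 158 × 2/24)/182 = 20.4%. With 5 h lost on each bad day the true loss is (24 × 5/24 + 158 × 2/24)/182 = 10.0%.

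**Sensitivity to how much is lost on a bad day (share of data recorded at removal):**

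| Hours lost per bad day | b = 0, k = 37 | b = 2/24, k = 24 |
|---|---|---|
| 5 | 95.8% | 90.0% |
| 12 | 89.8% | 86.2% |
| 24 | 79.7% | 79.6% |

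The first row is the boundary case. In the last row the rule removes men at about 20% true loss, as one would expect.

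**Other readings of the same sentence.**

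- *Only excluded days count, imputed gaps do not:* 37 days still cause removal (20.3%), but 24 days do not (24/182 = 13.2%).
- *Each lost hour counts once:* true losses of 4.2% and 10.0% are both under 20%, so neither man is removed.

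The 96% case therefore needs whole-day counting only. The 90% case needs whole-day counting and also needs imputed gaps to count.

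**Steady loss.** A man missing 4.5 h every day loses 4.5/24 = 18.75%. No day reaches 4.8 h and his total is under 20%, so he passes Data Exclusion. But he wears the band 19.5 h, short of the required 22 h, and exceeds the 2.4 h threshold in Study Setting. That threshold is itself inconsistent: 2.4/24 = 10%, whereas 20% of 24 h is 4.8 h.

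**The two removal rules.** Withdrawal Criteria counts non-use or misuse. Data Exclusion counts all missing plus excluded data. A man can pass one and fail the other, and either leads to loss of his data.

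**The case against.** The strongest reply is that the anomaly is read into the text. Missing data are said to be handled by imputation, so a filled gap may fairly be regarded as no longer missing; the 90% case then falls. If lost hours are what is counted, the 96% case falls too. Counting an excluded day in full is also coherent, because it tracks the data available for analysis, and any valid-day rule joined to a participant limit allows some reversal of order. A journal article may leave such conventions to the full protocol. The two 20% rules could serve different purposes, one adherence and the other data quality. Much of this stands: the percentages are conditional, and how to count an excluded day is partly preference.

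Two stronger readings are tempting and are not supported.

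- A reader might infer that a man with 90–96% of his data is removed while a man with 81% is kept. The first half is only possible, at the boundary and under unstated conventions. The second half holds under Data Exclusion alone, since that man breaches Study Setting and might fall under Withdrawal Criteria.
- A reader might project how many of 25 men would be lost. The documents give no distribution of over-limit days, and the SUD group's first 6 months are spent in a facility with a fixed schedule where staff synchronize the bands. No such number can be defended.

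One objection also bears on the remedy: a man kept without band inputs lacks a whole modality in a model meant to integrate all of them. That is a real cost, but not a reason to delete his other data.

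None of this answers the breadth of the deletion, which the article states as a rule and does not leave open.

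**Conclusion.** The point holds in a limited form. The participant limit is under-defined. On its literal reading it can remove a man with most of his band data recorded: about 96% or 90% at the boundary, about 90% or 86% with 12 h lost per bad day, and no material anomaly when bad days are wholly lost. These figures assume 182 days and full counting of excluded days; the second figure in each pair also assumes that imputed gaps count and that the full 2 h is lost on every ordinary day.

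Two parts do not depend on those assumptions. The daily and participant limits in Withdrawal Criteria, Study Setting, Digital Measurement of Biomarkers and Data Exclusion do not agree and must be reconciled. And a limit on band data deletes data that do not come from the band, in a sample that may be as small as 25 per group. The change is worth making while recruitment is open.

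**What to change.** 1. In both Data Exclusion and Withdrawal Criteria, state that when the band-data limit is passed only the band-derived inputs are dropped. Keep the demographic, psychological, craving and outcome data for the profiles and for models that do not need band features, except where the participant asks for his data to be removed. Changing one section alone would leave the other still discarding the same men's data.
2. Define the 20% total. Either state that imputed gaps do not count towards it, or count each lost or faulty hour once whether or not its day is excluded. The first option removes the 90% case only; the second removes both. Say explicitly how an excluded day is counted, and use the same numerator in both sections.
3. Reconcile the 22 h requirement, the 2 h anticipated loss, the 2.4 h threshold with its 20% label, and the 20% daily limit.

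The cost is wording. Some retained men will have noisier band averages or no band inputs, so the all-modality model will include fewer men than the other analyses; report both denominators.
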